### Target population and sample

The target population of the present study consisted of adults aged 20 to 59 years, representing the adult age group as defined by the Ministry of Health and the World Health Organization [40, 41], of both sexes, and experiencing depressive symptoms. The sample was intentional and non-probabilistic, comprising adult individuals with depressive symptoms residing in Florianópolis, within the aforementioned age range, and expressing interest in participating in the study.

### Inclusion criteria

Score ≥ 9 points on the Patient Health Questionnaire-9 (PHQ-9);Be aged between 20 and 59 years;Possess an electronic device with a camera and microphone, such as a computer, tablet, or cell phone;Have access to the internet;Be available for online and in-person meetings on specified days and times;Not be pregnant or in the postpartum period.

### Exclusion criteria

Require specialized psychiatric treatment, excluding cases of depression (e.g., psychosis, schizophrenia) based on self-reported diagnosis;Exhibit suicidal risk, as indicated by selecting the response options “a week or more” or “almost every day” in the PHQ-9 suicidal risk question;Have illnesses or physical limitations that impede participation in the study.

### Sample size, randomization, and allocation concealment

The sample size was calculated using G*power 3.1.9.2 software, and was based on an ANOVA model for repeated measures with three time points and two groups. Parameters included an average effect size of 0.25, statistical power of 80%, and 5% significance level for two-tailed tests, reaching a value of 28 individuals. Anticipating a potential dropout rate of up to 50%, the number calculated was doubled, bringing the total sample size to 56 individuals. Eligible individuals were randomly assigned to either the control group (CG), instructed to maintain their usual activities, or the intervention group (IG), which actively participated in the program. To ensure numerical and participant characteristic balance between groups, randomization was stratified by sex, age, and PHQ-9 score, employing a 1:1 ratio. The randomization process was executed using the online platform randomizar.org by researchers not directly involved in the intervention. The allocation list was concealed from all study evaluators.

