### Study variables

The primary outcome of the study was depressive symptoms and secondary outcomes were 24-h movement behaviors (physical activity, sedentary behavior, and sleep) and basic psychological needs (autonomy, competence, and relatedness). Autonomy, competence, and relatedness variables were also examined as potential mediators influencing the effectiveness of the intervention on depressive symptoms. Furthermore, sociodemographic factors, health conditions, self-perceived health, lifestyle, and factors related to the perception of barriers to practicing physical activity were considered as descriptive and/or adjustment variables.

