To verify the effect of the intervention on the primary outcome and secondary outcomes, per-protocol and intention-to-treat analyses will be conducted. The first one will take into account only IG participants who followed the activities until the last meeting, complied with the planned intervention protocol with at least 50% overall attendance and in each of the four blocks of the intervention, in addition to being duly evaluated in the line moments baseline and post-intervention. This decision aligns with the intervention proposal, in which the initial meetings comprised more theoretical activities, with practical sessions beginning in the second month onwards. Those from the GC who participated in the assessments will also be considered. The second analysis will include all individuals from the CG who participated in both data collections, and those from the IG considered in the per-protocol analyses. To fill in the missing data from the other participants, the multiple imputation technique will be applied, using sex, age, and the variables of interest as predictors. For comparisons between periods (pre- and post-intervention) and between groups (intervention and control), analysis will be conducted using generalized estimating equations (GEE), with Bonferroni post hoc adjustments. The significance threshold will be set at *p* ≤ 0.05. However, for time*group interactions, *p* ≤ 0.10 will be considered marginally significant [126]. Additionally, effect sizes will be calculated based on (a) Cohen’s d [127], considering small values (0.20 ≤ d < 0.50), medium values (0.50 ≤ d < 0.80), and large (d ≥ 0.80); and (b) partial eta squared (ηp2), with small (0.02 ≤ ηp2 < 0.13), medium (0.13 ≤ ηp2 < 0.26), and large (ηp2 ≥ 0.26) effect sizes [128]. These procedures will be performed using the Statistical Package for the Social Sciences (SPSS, version 23.0) software.

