**Fig. 4 Fig4:**
[figure not shown]
Description of the model of possible mediating variables of the Vincular Project. Source: own authorship (2023). Notes: total effect of the treatment on the investigative variable (coefficient “f”); mediated direct effect of the treatment on the investigative variable (coefficient “f’”); effect of treatment on basic psychological needs (“a” coefficients); effect of the treatment on the investigative variable, including the basic psychological needs variables (coefficients “a” and “b”)

The variables used in the models will take into account the difference between post-intervention and baseline values. The effect of the intervention on depressive symptoms will be observed directly, obtaining the total direct effect of the intervention. Subsequently, all paths for potential mediating variables will be included to determine the indirect effects of treatment on depressive symptoms. Two models will be tested: the first with the observed variables, represented by the overall PHQ-9 score and the individual autonomy, competence, and relatedness scores; and the second model, considering latent variables, corresponding to each PHQ-9 question and the basic psychological needs instrument. For statistical modeling, the “backward” selection strategy will be adopted, with a critical level of *p* ≤ 0.20 for variables to remain in the model. The following adjustment indices and cutoff points will be utilized: (a) degrees of freedom (df) ≥ 1; (b) chi-square *p*-value (X2) > 0.05; (c) ratio X2 per df < 3; (d) comparative fit index (CFI) and Tucker–Lewis index (TLI) > 0.90; (e) root mean square error of approximation (RMSEA) < 0.08; (f) RMSEA *p*-value < 0.05; and (g) standardized root mean square residual (SRMR) < 0.08 [132].

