It is also important to highlight the importance of monitoring indicators of depressive symptoms and 24-h movement behaviors after implementing these actions. Depression is associated with several functional disorders and, in some cases, symptoms may recur without appropriate follow-up. Adhering to and maintaining healthy behaviors is a challenge for a significant portion of the population, and this task can become even more difficult for those experiencing depressive symptoms. For the successful management of depression across its three phases—namely the beginning of treatment, continuation, and monitoring—interventions are required to discuss strategies and offer tools for maintaining positive results after the conclusion of this process. This ensures that the benefits persist in people’s daily lives. Moreover, when considering interventions aimed at behavioral changes with a focus on reducing depressive symptoms, it is clear that the satisfaction of basic psychological needs can be considered a key mediator of the expected results [36]. The inclusion of potential mediators in this research is crucial for understanding the mechanisms of change and the elements that can directly or indirectly impact a particular outcome. Information related to this subject favors the understanding of the psychosocial mechanisms involved in modifying behaviors, and consequently, the benefits related to mental health, contributing to improving the design of future interventions in this area. The Vincular Project also aims to achieve other results related to quality of life, such as aspects of health conditions, self-perceived health, and lifestyle. This holistic approach is justified by the need to understand the human being as a whole, complex, and susceptible to influences, while also having an impact on the environment in which they live. This information contributes to a comprehensive perspective on how the intervention can impact the health of adults with depressive symptoms, extending beyond the desired outcomes.

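### The stated GEE time-by-group contrast is in effect a change-score comparison; adjusting for baseline PHQ-9, sex and age would be a free gain in precision, with any other adjusters held to baseline values

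*Protocol article*

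**What the plan says.** - **Allocation** (Sample size, randomization, and allocation concealment): "randomization was stratified by sex, age, and PHQ-9 score, employing a 1:1 ratio". The cut-points for age and PHQ-9 are not given.
- **Effect analysis** (Data treatment and statistical analyses): for pre/post periods and the two groups, "analysis will be conducted using generalized estimating equations (GEE), with Bonferroni post hoc adjustments". The same paragraph sets a separate threshold for the time-by-group interaction, so that term carries the effect. No covariate is named. Sex and age are mentioned there only as predictors for multiple imputation.
- **Mediation models** (same section, text after Fig. 4): "The variables used in the models will take into account the difference between post-intervention and baseline values".
- **Possible adjusters** (Study variables): sociodemographic factors, health conditions, self-perceived health, lifestyle and perceived barriers "were considered as descriptive and/or adjustment variables". The timing of their measurement is not stated.
- **Intended results** (Discussion): "The Vincular Project also aims to achieve other results related to quality of life, such as aspects of health conditions, self-perceived health, and lifestyle". The last paragraph of the Introduction also classes lifestyle among the health-related outcomes.

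**The concern.** PHQ-9, sex and age were considered important enough to stratify on, yet none of them is named in the effect model. Baseline PHQ-9 enters that model as one of the two outcome values and not as a predictor. A change score fixes the weight on baseline at 1, whereas a baseline-adjusted model estimates it. In a trial planned on 28 completers, the efficiency given up could matter.

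There is also a labelling conflict. Lifestyle, self-perceived health and health conditions are listed both as things to adjust for and as things the intervention is meant to change. The lifestyle questionnaire has physical-activity and sleep domains, which the intervention targets directly. If post-intervention values of such variables were used as adjusters, part of the effect under test would be removed.

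**Working it through.** **1. The plan's own figure.** Inputs from the sample-size section: "Parameters included an average effect size of 0.25" (read here as Cohen's f), "based on an ANOVA model for repeated measures with three time points and two groups", and "statistical power of 80%, and 5% significance level for two-tailed tests, reaching a value of 28 individuals". The correlation rho is not stated. For the within-between interaction, lambda = f² × N × m / (1 − rho), with df1 = (k − 1)(m − 1) and df2 = (N − k)(m − 1). With f = 0.25, N = 28, m = 3, k = 2 and rho = 0.5, lambda = 0.0625 × 28 × 3 / 0.5 = 10.5 on 2 and 52 df, which gives power 0.812. So 28 reproduces at rho = 0.5, and 28 / (1 − 0.5) = 56.

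**2. What the GEE estimates.** In simulated complete pre/post data (28 participants, identity link, exchangeable working correlation), the time-by-group coefficient equalled the difference in mean change to within 1e-15. Adding sex and age as main effects altered neither the estimate nor its robust standard error (differences below 1e-14). Listing them as main effects in this model would therefore gain nothing.

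**3. Variance without stratification** (equal pre and post variances, in SD² units):
- post-intervention score alone: 1
- change score: 2(1 − rho) = (1 − rho²) + (1 − rho)²
- baseline-adjusted: 1 − rho²
- ratio of adjusted to change: (1 + rho)/2

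**4. Variance with PHQ-9 stratification.** Assume a normal baseline split at its median, balanced within halves. The baseline variance left within a half is 1 − 2/π = 0.363, so the true variance of the change contrast becomes (1 − rho²) + 0.363(1 − rho)². The adjusted variance stays at 1 − rho².

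| rho | change, nominal | change, stratified | adjusted | adjusted / nominal | adjusted / stratified |
|---|---|---|---|---|---|
| 0.3 | 1.40 | 1.09 | 0.91 | 0.65 | 0.84 |
| 0.5 | 1.00 | 0.84 | 0.75 | 0.75 | 0.89 |
| 0.7 | 0.60 | 0.54 | 0.51 | 0.85 | 0.94 |

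Simulations of the stratified design gave ratios of 0.82–0.84, 0.89–0.90 and 0.94–0.95.

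**5. Standard error.** At rho = 0.5 and 14 per arm, the nominal value is √(2 × 1.00/14) = 0.378 and the true value is √(2 × 0.84/14) = 0.346. Simulation gave 0.375 against about 0.350, with type I error near 3.5% (about 3% at rho = 0.3). This is for a pooled-variance t test. An uncorrected robust standard error is smaller by about √(13/14) = 0.96, which offsets part of the conservatism (0.375 × 0.96 = 0.36).

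**6. Power.** The assumed difference is 1.0 SD. That is what f = 0.25 would imply in a two-period, two-group layout (cell deviations of ±0.25 SD, so 4 × 0.25), but the protocol does not state it. Results for 14 per arm with the stratified design:

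| rho | change score | baseline-adjusted |
|---|---|---|
| 0.3 | 58–59% | 75–77% |
| 0.5 | 74% | 83% |
| 0.7 | 92% | 94% |

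The ranges cover separate simulation runs. If all 56 were retained (28 per arm, rho = 0.5, no allowance for stratification), power would be 95.7% against 98.9%.

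**7. Entry cutoff.** Inclusion requires a PHQ-9 score of at least 9, which narrows the baseline spread and leaves less to adjust for. A simulation that cut the baseline at its median, without stratification, gave ratios of about 0.85, 0.90 and 0.95.

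**The case against.** The stated analysis is valid: under randomisation the contrast is unbiased, and preferring covariate adjustment is a matter of efficiency. That stands, and it is why this is an improvement and not the correction of an error.

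Four stronger readings are tempting, and the documents do not support them:
- **The contrast gains nothing from baseline PHQ-9.** Relative to ignoring baseline, 2(1 − rho) is 1.4, 1.0 and 0.6 at rho = 0.3, 0.5 and 0.7. It breaks even only at 0.5, loses below that and gains above it. At 0.7 it removes 40% of the variance, against 49% with adjustment.
- **The plan needs 33% more participants than an adjusted one.** That is 1/0.75 at rho = 0.5 and describes unrestricted chance imbalance. Stratifying on PHQ-9 already limits that imbalance, so the variance ratio is nearer 0.89.
- **The sample size is wrong.** The 28 and 56 reproduce. They come from a three-time-point ANOVA, so the two-period power figures above cannot be set against its 80%.
- **The plan will adjust for post-randomisation lifestyle.** Study variables leaves open whether these variables are descriptive or adjusters, and when they are measured. Baseline use is a natural reading. Perceived barriers are not among the results named in the Discussion.

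It is also fair to say that a condensed article may leave the covariate set to a fuller plan, that no link function is stated, and that sex, age and the study variables enter the intention-to-treat analysis through imputation. These limit the point but do not remove it. The article does fix the form of the contrast and the use of differences in the mediation models, and main effects for sex and age would not change that contrast.

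**Conclusion.** The point holds as a free improvement. As stated, the effect analysis and the mediation models use baseline PHQ-9 less efficiently than baseline adjustment would at any correlation below 1 (equal variances assumed), and the stratification goes unused in the standard error. The cost is precision and some conservatism, not bias.

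At 14 per arm, the gain is about 17 to 18 percentage points of power at rho = 0.3, 9 at 0.5 and 2 at 0.7. It is smaller if more participants are retained or if the entry cutoff compresses baseline scores. These figures rest on an assumed correlation, a 1.0 SD difference, a median-split PHQ-9 stratum, complete data and an identity link, none of which the article states.

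The adjuster issue is conditional. The documents give the same variables two roles without fixing timing, and harm follows only if post-intervention values are used.

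**What to change.** 1. Model post-baseline PHQ-9 on arm (and arm by time if the six-month assessment is included), with baseline PHQ-9, sex and age as covariates. Alternatively, use a longitudinal model that constrains the baseline means of the two arms to be equal.
2. Use the same baseline-adjusted form for the secondary outcomes, and replace raw differences in the mediation models with post-intervention values adjusted for baseline.
3. State that any further adjuster is a baseline value. Treat post-intervention lifestyle, self-perceived health and health conditions only as outcomes.

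The cost is small, because baseline PHQ-9, sex and age are already collected. Trial status reports the trial as concluded, with the last assessment in November 2023, so this would be a change made after data collection. Date it, disclose it, and report the published GEE contrast as a sensitivity analysis.

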### Recruitment, screening, and selection

The sample recruitment process commenced after receiving approval from the CEPSH-UFSC. A comprehensive publicity strategy was implemented both online and in person. Initially, information was disseminated on the internet through social networks and email lists. Subsequently, posters were displayed at the Federal University of Santa Catarina, the University Hospital, and Basic Health Units, and letters were distributed to homes near the university. Additionally, the study was promoted through various channels, including a local program (TV UFSC), a television news segment featured in the “Jornal do Almoço,” a Brazilian television program aired by NSC-TV, an affiliate of Rede Globo, and a podcast called “Vem Cienciar.” Links to all these features were also made available online.

Those interested in participating in the Vincular Project could reach out through phone calls, WhatsApp messages, and emails. An initial registration process was facilitated via an online form-filling platform, allowing for the collection of identification information and a preliminary screening to verify compliance with eligibility criteria. Individuals who did not fit the requested profile were dismissed and those who met the pre-established criteria were invited to participate in a meeting for (a) guidance on the research objectives and procedures; and (b) completing additional questionnaires and receiving accelerometers. It is important to emphasize that the application of the informed consent form was administered prior to any data collection instrument. This form was made available online, enabling interested parties to review and express their agreement or refusal to participate in the research. Furthermore, at the conclusion of this session, the term, initialed and signed by the responsible researcher, was made available for download, as mentioned before.

It is noteworthy that psychoeducational materials on mental health were made available and referrals were provided to those who were not included in the research and who presented a degree of suicidal risk. During all phases of the research, other support materials were also furnished. These included the Brazilian Guide to Physical Activity, which presents comprehensive guidelines for engaging in physical activity and addressing sedentary behaviors in a didactic manner. Moreover, a compilation of tools for recognizing and treating depression, published by the Brazilian Medical Association in the Brazilian Journal of Psychiatry, was supplied. Informative manuals and booklets focusing on mental health, disseminated by the World Health Organization, the Pan-American Health Organization, the Ministry of Health, and the Brazilian Psychiatric Association, were also distributed. All individuals interested in volunteering for the research and who passed the screening of the eligibility criteria were welcomed in the same way, receiving all the necessary guidance and direction, based on their individual responses.

### Assessments

The assessment of the variables of interest was carried out at three moments: (a) baseline pre-intervention (January 2023); (b) post-intervention, immediately following the conclusion of the program (May 2023); and (c) post-intervention, 6 months after the end of the intervention (follow-up evaluation, conducted in November 2023). Questionnaires were employed to measure the variables, and participants were required to respond in the presence of a previously trained researcher. To facilitate this process, specific dates and times were scheduled based on participants’ availability. Furthermore, during these assessment periods, participants used accelerometers to objectively measure their 24-h movement behaviors. In Fig. 1, it is possible to observe a schematic diagram with the time schedule of enrolment, interventions, and assessments.

**Fig. 1 Fig1:**
[figure not shown]
Study design flowchart. Source: own authorship (2023)

### Theoretical basis of the Vincular Project

Various program frameworks and behavior change theories have contributed to the development of the intervention. The Self-Determination Theory, formulated by Edward L. Deci and Richard M. Ryan in 1981, emphasizes the socio-contextual conditions that either facilitate or impede the natural processes of self-motivation and healthy psychological development [33]. This theory is grounded in an approach to motivation and human personality that employs traditional empirical methods by applying an organismic metatheory (explained below), which highlights the importance of the internal resources of human beings in order to enable personality development and behavioral self-regulation [33, 42]. One of the main objectives of the theory has been to offer a more specific focus on motivation, seeking to understand what type of stimulus is being manifested at a given moment or driving a particular behavior [33].

In this context, Self-Determination Theory focuses on differentiating between self-determined (also known as autonomous) and non-self-determined (or controlled) forms of motivation, which reflect the extent to which actions are fully endorsed by the individual [33]. Self-determined motivation pertains to reasons or motives for engaging in a behavior or achieving a specific goal that are self-endorsed. Individuals driven by autonomous motives perceive their actions as freely chosen and aligned with their personal beliefs, values, and goals [43]. Conversely, non-self-determined motivation encompasses reasons for action that are not self-endorsed. In this case, individuals who report controlled reasons for their actions perceive their behaviors as originating from external sources, being controlled by external circumstances or contingencies [44, 45]. There is a third form of regulation called amotivation, which consists of the lack of any motivational force to act. Individuals experiencing amotivation do not recognize any clear reason, motive, or intention behind their actions [32, 46]. It is evident, therefore, that motivation can be influenced and directed by numerous internal and external factors, each with varying effects on individuals’ behavior [47].

In order to detail the different forms of motivation and the contextual factors that facilitate or impede the internalization and integration of the regulation of these behaviors, Deci and Ryan [35] developed a subtheory within Self-Determination Theory, known as organismic integration theory. This theory delineates a continuum of self-determination wherein amotivation, or the absence of intent to act, resides at the left end. As previously mentioned, unmotivated individuals either abstain from action or engage without any underlying motivation, merely going through the motions. Moving along the continuum, there is the extrinsic motivation originating from external sources. This type of motivation involves performing an action to attain a separable outcome and lacks inherent satisfaction from the activity itself. Extrinsic motivation can be categorized based on four regulatory styles. External regulation encompasses less autonomous behaviors performed to meet an external demand or respond to a reward or threat. Introjected regulation reflects the acceptance of a regulation, albeit not entirely internalized, wherein behaviors are executed to alleviate guilt or anxiety or to boost one’s ego, maintaining a sense of value, such as pride. The third type of extrinsic motivation is identified regulation, which reflects a conscious appreciation of a goal or behavioral regulation, leading to the acceptance or acknowledgment of the action as personally important, beneficial, and useful. Finally, integrated regulation is characterized as the most autonomous form of extrinsic motivation, in which behaviors are assessed and recognized as significant and consistent with other values and needs. It is noteworthy that external and introjected regulations together constitute a composite of controlled (non-self-determined) motivation, while identified and integrated regulations have autonomous (self-determined) components. At the far right of the continuum, intrinsic motivation corresponds to a process characterized by personal choice, satisfaction, and pleasure.

Another assumption of Self-Determination Theory is that the level and quality of motivation experienced by individuals during the performance of an action are determined by the perceived value of that action in satisfying three fundamental psychological needs: autonomy, competence, and relatedness [32, 34]. Autonomy refers to actions that are self-endorsed, freely chosen by the individual, leading to a sense of ownership and personal responsibility. Competence corresponds to the perception of effectiveness in interactions with the environment, of mastering and expanding your capabilities and skills, making them challenging, until personal growth is achieved. The relatedness revolves around the desire for belonging, close emotional relationships, and the need to feel accepted and respected, fostering a sense of connection and mutual concern. It is evident that these basic psychological needs are innate and intricately linked to intrinsic motivation, self-regulation, and overall well-being. They explore the processes and conditions that facilitate healthy development and effective functioning of the individual [32]. Additionally, it is highlighted that these psychological needs are interdependent, suggesting that “the satisfaction of one need supports the satisfaction of the other two needs” [34].

Whether an individual’s basic psychological needs are satisfied or frustrated depends on the extent to which the subject’s environment and relationships support or harm these needs [34, 35]. Behaviors or messages from social agents (such as health professionals, family, friends, and colleagues), who operate within an individual’s social environment, or information obtained through various channels like magazines, newspapers, or social networks, can contribute to changes in psychological needs [36]. For example, if these behaviors, messages, or content support the satisfaction of psychological needs, individuals will presumably experience their actions as autonomously motivated, enabling the engagement and/or maintenance of health behaviors [34–36].

On the other hand, behaviors, messages, or content that do not support or impede the satisfaction of psychological needs may possibly harm autonomous motivation. This, in turn, can favor controlled (non-self-determined) forms of motivation or amotivation, potentially contributing to maladaptive results and behavioral disengagement [34–36]. Teixeira and collaborators [36] state that “guidance on the behaviors displayed by social agents, and specifying the content of messages, are potentially effective means to promote autonomous motivation and sustained behavior change.” They also emphasize the importance of understanding how these interventions influence the quality of motivation through the satisfaction of the three basic psychological needs. From this perspective, the satisfaction of basic psychological needs may be considered an important mediator of interventions based on the Self-Determination Theory on health outcomes, especially behavior change, reflecting both mental and physical aspects [36].

Ryan and Deci [33] offer additional examples of how basic psychological needs can influence the different regulations of extrinsic motivation. Since extrinsically motivated behaviors are not typically interesting, it becomes clear that many individuals engage in actions based on their connection to or desire for connection with people close to them. These individuals feel a sense of connection or relationship with others who request, model, or value these behaviors. This suggests that the relatedness, the need to belong, is a crucial element for internalization. Perceived competence also plays a role in the relative internalization of extrinsically motivated activities, as individuals tend to adopt activities or behaviors valued by social groups when they perceive themselves as capable and effective in relation to those activities. To complete the triangle of psychological needs, autonomy supports internalization and, in particular, is a critical component for the integration of regulation.

Demonstrations of positive results associated with Self-Determination Theory can be observed in different behaviors, contexts, and populations. A systematic review with the aim of investigating the relationships between constructs based on Self-Determination Theory and the behavioral outcomes of exercise and physical activity revealed a positive association between more autonomous forms of motivation and exercise [48]. Furthermore, competence satisfaction and more intrinsic motives positively predict exercise involvement in several samples [48]. In a meta-analysis of randomized clinical trials, it was possible to identify significant albeit small effects for physical activity, sedentary behavior, diet, alcohol consumption, and smoking cessation [49]. Another study, developed in Norway, examined, based on Self-Determination Theory, how maladaptive motivational processes at work are related to sleep disorders and mental health problems [50]. The findings indicated that participants were more likely to report sleep disturbances, anxiety, and depressive symptoms when feeling frustrated in relation to basic psychological needs for autonomy, competence, and relatedness in the workplace [50]. In other words, the stronger the psychological needs for a given behavior, the more robust the self-determined motivation to perform it. However, there is a gap in the literature concerning the applicability of the Self-Determination Theory in clinical trials specifically targeting 24-h movement behaviors in adults with depressive symptoms. Additionally, there is a need to investigate autonomy, competence, and relatedness as potential mediators associated with the effectiveness of these interventions.

More recently, an expert consensus study [36] and a meta-analysis [37] were carried out in order to identify and classify techniques used to promote the satisfaction and motivation of basic psychological needs in health interventions supported by Self-Determination Theory. This is because, although the effects found from these interventions are effective in motivating the adoption and maintenance of health-related behaviors, as well as promoting adaptive psychological outcomes, there is still considerable variability in the application of the theory in these contexts [36, 37]. Teixeira and colleagues [36] developed a final classification comprising 21 motivation and behavior change techniques, with each technique organized according to the most closely related construct of satisfying psychological needs. The authors also highlighted “a considerable interrelatedness among the motivation and behavior change techniques and the underlying constructs they are proposed to change” [36]. Gillison et al. [37], based on the analysis of 74 intervention studies, identified that the techniques currently in use had the potential to cause changes in the theoretical mediators of health behavior, with a large effect size for autonomy and support for autonomy, moderate for the need for competence, and small for relatedness and motivation. Greater competence satisfaction was observed in individual interventions, when compared to group interventions, and for adults than for children [37]. The results and discussions presented provide support to (a) improve the consistency in the descriptions of interventions based on the Self-Determination Theory, providing social agents, whether researchers, interventionists, or health professionals, with a set of pre-established terms, definitions, and comprehensive approaches that facilitate understanding and precision of the approaches used [36, 37]; and (b) conduct more expressive and pertinent comparisons of interventions based on the components they incorporate, enabling the identification of the most promising techniques for achieving more effective behavior changes [51].

From the content presented, it is evident that the Self-Determination Theory can help to better understand the reasons that lead individuals to adopt to and maintain health-related behaviors, making it a valuable tool for interventions in this context. The premise is that fulfilling basic psychological needs can enhance intrinsic motivation, thereby influencing behavior change. Thus, according to the creators of the Self-Determination Theory, “[…] research on the conditions that foster versus undermine positive human potentials has both theoretical import and practical significance because it can contribute not only to formal knowledge of the causes of human behavior but also to the design of social environments that optimize people’s development, performance, and well-being” ([32, 33], p.68).

